### Sample size

The target sample size is 6050 (3025 per group), obtained from 50 practices (25 per randomised group) with an average cluster size of 121 patients per practice. This is estimated to provide 80% power to detect a ratio of the group proportions (or relative risk) of 0.75. This sample size assumes a control group readmission rate of 35% based on a recent Australian cohort study (*n* = 6172) reporting an atherothrombotic disease readmission rate of 35% at 2 years for patients with CHD [28]. The estimation assumes a significance level of 0.05 and an intra-class correlation coefficient (ICC) of 0.05. The ICC is based on data from two cross-sectional studies in Australian primary care [29, 30]. Loss to follow-up is anticipated to be very minimal given the primary outcome will be obtained via data linkage [26].

### Statistical analyses

Analyses will be conducted at the individual level while accounting for clustering of patients within practices. Intention-to-treat principle will be followed with patients analysed according to their randomisation group. Differences in the proportion of patients who are hospitalised (as well as binary secondary outcomes) will be analysed using log-binomial regression or robust Poisson regression in case of convergence issues. Clustering will be accounted for by modelling the correlation among patients from the same cluster using generalised estimating equations with an exchangeable correlation structure. Sensitivity analyses will include analyses of yearly rates using Poisson regression and/or time-to-event analyses via Cox models. Adjusted analyses will also be performed to account for baseline imbalances in cluster and patient characteristics. Pre-specified sub-group analyses will be used to determine the impact of the intervention on different patient groups (male v female; low SES v high SES, different CVD subgroups, influenza vaccination or not) and practice types (e.g., large v small and urban v rural). This will be done by adding the subgroup variable as well as its interaction with the intervention to the main analysis model. As data will be extracted from primary care practice clinical records and administrative data, if not recorded, it will be assumed that the task has not been done. A detailed analysis plan including mock tables will be developed and signed-off prior to unblinding.

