### Randomisation

Practices will be randomised 1:1 to intervention (collaborative quality improvement program) or control groups using a computer-generated sequence generated with SAS 9.4 (Proc Surveyselect). Randomisation will be stratified according to two subgroups - rural versus urban location and size of the practice (≤2 versus > 2 GPs in a practice). The statistician performing randomisation will be blinded to practice names and details and only exposed to the practice characteristics that enable stratification. Once allocation is completed, a research team member will be provided the allocation list to enable communication with practices and commence arrangements for their respective requirements. It is not be possible to conceal the group allocation from the practices themselves or the research team delivering the intervention. However, given data is collected via linkage and not performed by research staff, it is essentially concealed. The statistician conducting analysis will be blinded to practice allocation.

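### The main model as described omits the two factors used to stratify randomisation; if they predict hospitalisation, the primary analysis is valid but conservative and gives up precision

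*Protocol article*

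**What the plan says.** The Randomisation section of the protocol article states: "Randomisation will be stratified according to two subgroups - rural versus urban location and size of the practice", with practice size split at two GPs. That makes four strata.

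The Statistical analyses section says that the primary outcome and the binary secondary outcomes "will be analysed using log-binomial regression or robust Poisson regression in case of convergence issues". Clustering is handled by GEE with an exchangeable working correlation by practice. No covariate is named for this model.

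Two further sentences in that section bear on whether the strata are in it:

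- "Adjusted analyses will also be performed to account for baseline imbalances in cluster and patient characteristics".
- Subgroups, which include practice size and urban/rural location, are to be examined by putting the subgroup variable and its treatment interaction into the main model.

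The section ends by announcing a detailed analysis plan, to be signed off before unblinding.

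The Sample size section states: "The target sample size is 6050 (3025 per group), obtained from 50 practices (25 per randomised group) with an average cluster size of 121 patients". It continues: "This is estimated to provide 80% power to detect a ratio of the group proportions (or relative risk) of 0.75", with a control rate of 35%, a significance level of 0.05 and "an intra-class correlation coefficient (ICC) of 0.05". It does not mention stratification.

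**The concern.** Stratified allocation balances location and practice size between the arms, so differences between strata largely drop out of the true variability of the treatment effect estimate. A model without the strata leaves those differences in the residual between-practice variation, and they enter the reported standard error. When the strata are prognostic, the result is a confidence interval that is too wide and a test that rejects too seldom under the null.

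This could matter here because there are only 50 practices and, at an ICC of 0.05, most of the variance of a practice proportion lies between practices.

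The adjusted analyses do not clearly repair it. They are additional to the main analysis and are directed at baseline imbalance, and these two factors are the ones that the design itself keeps balanced. The reason to adjust for them is that they shaped the allocation.

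**Working it through.** **Inputs from the Sample size section.** Control proportion 0.35; RR 0.75, so intervention proportion 0.35 × 0.75 = 0.2625; ICC 0.05; 121 patients per practice; 25 practices and 3025 patients per arm; significance level 0.05, power 80%. Sidedness is not stated. Two-sided is assumed, because a one-sided test would need only about 2380 per arm.

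**Input not in the documents.** R², the share of between-practice variance that the strata explain. Range assumed: 0 to 0.30.

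**Step 1: reproduce the plan's figure.** Individual-level n per arm = (0.35×0.65 + 0.2625×0.7375) × (1.960 + 0.842)² / 0.0875² = 431.7. Design effect = 1 + 120 × 0.05 = 7.0. Product: 3022 per arm (3045 with pooled variance), against 3025 stated. Power at 3025 per arm is 79.8%. The full ICC is used, so no gain from stratification is built in.

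**Step 2: design effect with the strata removed.** DE(R²) = 0.95 + 121 × 0.05 × (1 − R²) = 0.95 + 6.05 × (1 − R²). The unadjusted model reports a standard error based on 7.0, while the true one follows DE(R²). Hence:

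- Reported/true SE = √(7.0 / DE(R²)).
- Type I error, unadjusted = 2 × [1 − Φ(1.96 × reported/true SE)].
- Power, unadjusted = Φ[(0.0875 − 1.96·s0) / (s1 × true/reported SE)], where s0 and s1 are the pooled and unpooled standard errors at effective n = 3025/7.0.
- Power, adjusted: the ordinary formula at effective n = 3025/DE(R²).

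Example at R² = 0.20. DE = 0.95 + 4.84 = 5.79 and SE ratio = √(7.0/5.79) = 1.100. Unadjusted, with s0 = 0.0314 and s1 = 0.0312: Φ(0.92) = 82.0%. Adjusted, with effective n = 3025/5.79 = 522: Φ(1.11) = 86.7%.

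| R² assumed | DE(R²) | Reported/true SE | Type I, unadjusted | Power, unadjusted | Power, adjusted | Points forgone |
|---|---|---|---|---|---|---|
| 0 | 7.00 | 1.00 | 5.0% | 79.8% | 79.8% | 0 |
| 0.05 | 6.70 | 1.02 | 4.5% | 80.3% | 81.5% | 1.2 |
| 0.10 | 6.40 | 1.05 | 4.0% | 80.9% | 83.2% | 2.3 |
| 0.20 | 5.79 | 1.10 | 3.1% | 82.0% | 86.7% | 4.7 |
| 0.30 | 5.19 | 1.16 | 2.3% | 83.4% | 90.1% | 6.7 |

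With 200 patients per practice (10,000/50, the figure in the abstract) the pattern is the same: 83.1% to 85.4% at R² 0.10, and 84.4% to 88.8% at R² 0.20.

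**Step 3: what an R² means in hospitalisation rates.** Between-practice variance = 0.05 × 0.35 × 0.65 = 0.01138. Variance of a practice proportion = 0.01138 + 0.95 × 0.2275/121 = 0.01316. An 8-point gap between two strata of equal size contributes 0.08²/4 = 0.0016. That is 12% of practice-mean variance (14% of between-practice variance), giving SE inflation 1/√(1 − 0.12) = 1.067 and type I error 3.7%. With a 90/10 split the same gap contributes 0.08² × 0.09 = 0.00058, or 4%, giving SE inflation about 1.02 and type I error about 4.5%. The documents give neither the gaps nor the splits.

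**Step 4: simulation.** 50 practices of 121 patients in four strata, stratified 1:1 allocation, 6000 runs per scenario, analysed on practice proportions. The adjusted comparison is a linear model with both factors.

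| R² | Type I: sandwich z, uncorrected | Type I: unadjusted, t-corrected | Type I: adjusted | Power: unadjusted, t-corrected | Power: adjusted |
|---|---|---|---|---|---|
| 0 | 6.5% | 5.2% | 5.3% | 84.6% | 84.1% |
| 0.10 | 4.3% | 3.4% | 4.2% | 85.4% | 87.0% |
| 0.20 | 4.1% | 3.3% | 5.2% | 86.8% | 90.2% |
| 0.30 | 2.8% | 2.0% | 4.8% | 87.0% | 92.4% |

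At R² 0.20 under the null, the mean estimated SE of the log ratio was 0.093 against a true 0.085. Power levels exceed the formula because the simulation multiplies each intervention practice's rate by 0.75, which shrinks between-practice variance in that arm. The comparison between columns is what counts. It agrees in direction, with somewhat smaller gains (about 1.6, 3.5 and 5.5 points at R² 0.10, 0.20 and 0.30).

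**The case against.** **Covariates are commonly left to the analysis plan, and one is promised.** This has weight. No sentence says outright that the main model is unadjusted, and the subgroup sentence is a general recipe that also covers sex, SES, CVD subgroup and vaccination. But the article does more than stay silent. It makes adjustment additional and ties it to imbalance, and it has location and practice size put into the main model for the subgroup tests. The natural reading is that the strata are not there already. Location and practice size could fall under the cluster characteristics of the adjusted analyses, but that would still leave them out of the primary result.

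**The harm rests on inputs that the documents do not give.** This stands in full. If the strata do not predict hospitalisation, nothing is lost. If one stratum holds few practices, even a sizeable gap costs little.

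**The named method may err the other way.** This stands in part. With 50 practices and no small-sample correction, the sandwich z-test had a type I error of 6.5% at R² = 0. From R² 0.10 upward it was already below 5%, so the offset is partial. It is also a separate matter, and not one to rely on for cancellation.

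**A stronger reading to resist.** A reader might infer that the standard errors are certainly too large and that the trial falls short of its 80% power. The documents support neither. The first depends on an unknown R². The second fails because 6050 reproduces from the full ICC, so planned power does not rely on stratification. Unadjusted power in fact rises slightly with R² (79.8% to 83.4%).

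**Conclusion.** The concern holds conditionally. As described, the main model does not reflect the stratified randomisation. If location and practice size are prognostic, the primary analysis stays valid, with no bias and no excess of false positives from this source, but it is conservative and less precise than the design allows.

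The cost is nil at R² = 0, about 1 to 2 power points at R² 0.05 to 0.10, and about 5 to 7 points at R² 0.20 to 0.30. Over the whole range the standard error is 0 to about 16% too large and type I error falls from 5.0% to about 2.3%. What is forgone is extra precision beyond the planned 80%.

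These figures assume a two-sided test, equal practice sizes, ICC 0.05 and the stated R² range. They apply to the primary outcome. The same reasoning extends to the secondary outcomes, but no size was computed for them. Confidence is good on the omission and its direction, and low on its exact size.

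**What to change.** State, in the analysis plan at the latest and before unblinding, that the primary log-binomial or robust Poisson GEE model and the corresponding secondary outcome models include rural/urban location and practice size (≤2 v >2 GPs) as fixed effects. Report the model without them as a sensitivity analysis. Keep the adjustment for other baseline characteristics as a separate, additional analysis.

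The cost is one sentence and two practice-level terms, that is, two degrees of freedom among 50 practices. Both variables are known for every practice at randomisation, so no data collection is needed. If the extra terms cause convergence trouble, the robust Poisson fallback is already in the plan. Naming the terms in advance also removes any later choice between an unadjusted and an adjusted primary result.

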### Intervention and control groups

Practices allocated to the intervention will participate in a CHD secondary prevention collaborative quality improvement program. The program is designed to use data and practice level engagement to implement rapid and progressive changes based on Plan, Do, Study, Act (PDSA) cycles for pre-determined performance targets [21]. The program is underpinned by the psychology of behaviour change, active practice-level engagement combined with extraction and utilisation of electronically extracted data from practice software [12]. Practices will collaborate and support each other between and within practices in an ongoing way over 12 months to achieve a set of key performance measures (Table 1). These measures have been pre-determined based on guidelines [6] and availability of data for extraction and were developed and approved through an iterative process involving study investigators, clinicians and quality improvement experts. Intervention practices will receive their summarised performance data monthly.

**Table 1 Tab1:** QUEL intervention key performance measures

• Proportion of patients with CHD where LDL has been recorded within the previous 12 months	
• Proportion of patients with CHD whose most recent LDL result was less than 2.0 mmol/L	
• Proportion of patients with CHD with a recorded BP reading taken within the previous 12 months	
• Proportion of patients with CHD whose most recent BP reading, taken within the previous 12 months, was less than or equal to 130/80 mmHg	
• Proportion of patients with CHD whose smoking status has been recorded	
• Proportion of patients with CHD recorded as a current smoker	
• Proportion of patients with CHD who are currently prescribed an anti-platelet agent	
• Proportion of patients with CHD who are currently prescribed a statin	
• Proportion of patients with CHD who are currently prescribed an ACE inhibitor or ARB	
• The proportion of patients with CHD with MBS Items 721 or 732 claimed (GP Management Plans or review)	
• Proportion of patients with CHD who have an influenza vaccination recorded within the previous 12 months	

*CHD* Coronary heart disease, *LDL* Low density lipoprotein, *BP* Blood pressure, Angiotensin-converting-enzyme (ACE) inhibitor, *ARB* Angiotensin II receptor blockers, *MBS* Medicare Benefits Scheme, *GP* General practice

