### Outcomes

The primary outcome is the proportion of patients with unplanned CVD hospitalisations within 2 years of baseline data extraction (and commencement of intervention for those allocated to intervention group). For this study, CVD is defined as any condition involving the heart, brain or peripheral blood vessels and includes CHD (such as angina and myocardial infarction, MI), cerebrovascular disease (such as stroke), peripheral arterial disease and other conditions including heart failure and atrial fibrillation [25].

Secondary outcomes, also at 2 years) are;
i.Proportion of patients with major adverse cardiac and cerebrovascular events (fatal and non-fatal) that includes CHD (angina or MI), stroke or CVD death,ii.proportion of patients who received guideline-recommended medicines,iii.proportion of patients with a chronic disease management plan or review (Australian Medicare Item numbers 721 or 732 respectively) and;iv.proportion of patients achieving national targets for CVD risk factors (total cholesterol, systolic blood pressure, smoking).

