### Data collection and management

All data will be collected at baseline, 12 and 24 months. CVD hospitalisations and cardiovascular events will be collected via state-based administrative admissions data (depending on location of recruited practices). Individual patient deaths will be collected via linkage with the National Death Index and medication prescriptions and health service utilisation via linkage with the Australian Government Department of Health Pharmaceutical Benefits Scheme (PBS) and Medical Benefits Scheme (MBS) schemes respectively. Probabilistic matching will be used to link records and the estimated proportion of invalid and missed links using data linkage will be very low [26]. Data collection pertaining to the proportion of patients with chronic disease management plans and achieving national risk factor targets (cholesterol, smoking, and BP) will be electronically extracted from participating practice software systems using an automated data extraction tool with encrypted identifiers attached to patient data.

All data will be stored on a password-protected Secure Unified Research Environment (SURE), which is a purpose-built, remote-access data storage facility. This environment allows researchers to safely access, store and analyse study data [27]. Only aggregated and analysed data can be exported and data in SURE cannot be copied, downloaded or transmitted by email or other means. Only trained study research staff will have access to the SURE facility through a staff-specific username and password. The linked dataset will therefore be anonymised and the research team who will be analysing the data and delivering the intervention will not have access to individual-level data. This maximises privacy and forms an important aspect of the requirements for waiver of consent approval. Electronic files containing linked data for analysis will be stored on a Virtual Project Workspace within SURE and the access period shall be from study commencement for 7 years to enable all analyses to be completed. At the end of this data retention period, the tapes holding the archived data files will be physically destroyed.

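### Scoring unrecorded values as failures multiplies cholesterol and blood pressure target attainment by the recording rate, which the intervention itself sets out to raise

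*Protocol article*

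**What the plan says.** The last secondary outcome, measured at 2 years, is the "proportion of patients achieving national targets for CVD risk factors (total cholesterol, systolic blood pressure, smoking") (Outcomes). Under Data collection and management, these values "will be electronically extracted from participating practice software systems using an automated data extraction tool". They do not come from linkage.

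Statistical analyses gives one rule for absent entries: "if not recorded, it will be assumed that the task has not been done". It does not separate process items from measured targets. The sensitivity analyses named there are yearly rates by Poisson regression and Cox models, and neither concerns unrecorded risk factors.

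Table 1 (Intervention and control groups) lists the intervention's performance measures. Three of them are about recording:
- "Proportion of patients with CHD where LDL has been recorded within the previous 12 months"
- "Proportion of patients with CHD with a recorded BP reading taken within the previous 12 months"
- "Proportion of patients with CHD whose smoking status has been recorded"

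The same section adds: "Intervention practices will receive their summarised performance data monthly". Control practices have usual care without the programme.

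Randomisation states that allocation cannot be hidden from practices, but argues that "given data is collected via linkage and not performed by research staff, it is essentially concealed".

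**The concern.** The rule is sensible for a process item. If no prescription or care plan is on file, counting it as not done is a reasonable convention. Being at a cholesterol or blood pressure target is different: a patient with no value has an unknown status, and the rule turns that into a failure.

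This would matter less if recording were equal in the two arms. Here one arm is coached and given monthly data partly in order to raise recording, and the other is not. Extra recording moves some patients who were already at target from failure to success. With target status fixed, it can never move anyone the other way. The error therefore has one direction, towards the intervention.

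What is at stake is the interpretation. Better risk-factor control is part of the stated aim, and the Discussion expects to report the effect on risk factor levels. A difference in charting could be reported as a difference in cardiovascular risk.

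**Working it through.** **Inputs from the protocol (Sample size):** 3025 patients per arm, 121 per practice, 25 practices per arm, ICC 0.05, alpha 0.05 (taken as two-sided), control rate 35%, relative risk 0.75, power 80%.

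**Assumptions, not in the protocol:** recording rates by arm; the true share at target (50% in both arms, so no true effect); recording unrelated to target status; recording of LDL bringing total cholesterol with it.

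**Step 1: reproduce the plan's own figure.** Design effect = 1 + (121 − 1) × 0.05 = 7. With 35% v 26.25% and unpooled variance, n = (1.960 + 0.842)² × (0.35 × 0.65 + 0.2625 × 0.7375) / 0.0875², which gives 432 per arm. Multiplying by 7 gives 3024 per arm, or 6048 in total, against the stated 6050. The figure reproduces. It concerns the primary outcome and is used here only to fix the effective size: 3025 / 7 = 432.1 per arm.

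**Step 2: effect of the rule.** Let T be the true share at target and r the share recorded. If unrecorded means not at target, observed attainment = T × r. With the same T in both arms, the observed relative risk is r(intervention) / r(control), whatever T is. An analysis that did not score unrecorded values as failures would give 1.00 under these assumptions.

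**Step 3: chance of a false significant benefit.** P = Φ(d/SE − 1.960), where d is the observed difference and SE = √[(p₁(1 − p₁) + p₂(1 − p₂)) / n_eff]. For 80% v 90% recorded: p = 0.40 v 0.45, SE = √(0.4875 / 432.1) = 0.0336, d/SE = 1.489, P = Φ(−0.471) = 32%.

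Higher ICCs are included because recording is practice behaviour and may cluster more than hospitalisation. Design effects are 7, 13 and 19, and effective sizes are 432.1, 232.7 and 159.2 per arm.

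| Recorded, control v intervention | Observed at target | RR | ICC 0.05 | ICC 0.10 | ICC 0.15 |
|---|---|---|---|---|---|
| 90% v 95% | 45.0% v 47.5% | 1.06 | 11% | 8% | 7% |
| 80% v 90% | 40.0% v 45.0% | 1.13 | 32% | 19% | 15% |
| 70% v 85% | 35.0% v 42.5% | 1.21 | 62% | 38% | 28% |
| 60% v 80% | 30.0% v 40.0% | 1.33 | 87% | 62% | 47% |

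The chance expected by design of a significant result in this direction, with no true effect, is 2.5%.

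**Step 4: other inputs.** With 30% truly at target, the 70% v 85% case gives 21.0% v 25.5% and P = 35%. The approximate cohort of 10,000 (200 per practice, design effect 1 + 199 × 0.05 = 10.95, effective size 5000 / 10.95 = 456.6) barely changes the ICC 0.05 results: 62% becomes 64% and 87% becomes 89%.

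**Step 5: smoking.** Assume 15% true smokers and recording of 80% v 90%. If unrecorded means not at target, attainment is 0.85 × 0.80 = 68.0% v 0.85 × 0.90 = 76.5%, a false benefit. If unrecorded means not a smoker, recorded smokers are 12.0% v 13.5%, a false harm. The protocol does not say which coding applies to the outcome.

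**The case against.** The strongest reply is about scope. The rule speaks of a task, which fits a prescription, a plan or a test better than a blood pressure below a threshold. A detailed analysis plan is still to be signed off before unblinding and may draw that line. This is fair, and part of the remedy is simply to state the scope. But the sentence covers the extracted data without exception, and the article gives no other rule for an unrecorded target value.

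The second reply is that the size rests on chosen inputs. That stands. The protocol contains no recording rates. If recording is already high, the artefact is small. The programme lasts 12 months and the outcome is at 2 years, so the gap has to survive a year after the programme ends. Table 1 concerns LDL while the outcome is total cholesterol. Differential recording is a likely consequence of the design, not an established fact.

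Third, documented attainment is a legitimate quality-improvement measure, and the alternatives have their own weaknesses. An analysis of recorded patients conditions on something that happens after randomisation, and imputation rests on an untestable missing-at-random assumption. This is why the remedy shows two analyses and does not replace one with the other.

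A reader might also infer several stronger things that the article does not support:
- That the outcome becomes purely a measure of recording. It becomes recording times control, so it still carries information on control.
- That patients who died or left, or whose practice withdrew, are scored as failures. This is not stated, and who enters the 24-month denominator is ordinary analysis-plan content.
- That the Table 1 measure on current smokers fixes the opposite coding for smoking. It is a feedback measure and does not say how unrecorded patients are classified in the trial outcome.

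**Conclusion.** The point holds for the cholesterol and blood pressure targets in the last secondary outcome. Followed as written, the rule can produce a benefit with no change in any patient's control, because the intervention targets the factor by which true attainment is multiplied. With 50% truly at target in both arms, 3025 per arm and ICC 0.05, the false-benefit probability is about 11%, 32%, 62% or 87% across the four recording gaps considered. All of these rest on assumed recording rates, and they fall with a higher ICC or a fading gap. For smoking the direction cannot be settled from the article.

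The concealment statement does not hold for these outcomes. They come from practice software and are entered in practices that know their allocation.

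It would be wrong to extend this to the trial's main result. Hospitalisations, cardiovascular events and deaths come from linkage and do not depend on what practices record. One secondary outcome is affected and the remedy is cheap, so this is something that should be fixed, not a fault that undermines the trial.

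**What to change.** 1. Limit the rule that unrecorded means not done to process outcomes, such as a prescription or a care plan.
2. Report the proportion of patients with a recorded value, by arm, as a result in its own right for cholesterol, blood pressure and smoking status.
3. State how unrecorded smoking status is coded in the outcome.
4. For the risk-factor targets, present two analyses: one counting unrecorded as not at target, labelled documented attainment, and one that does not score unrecorded values as failures, for example multiple imputation that respects practice clustering and uses baseline values. Claim improved risk-factor control only if the two agree.
5. Restrict the concealment statement under Randomisation to outcomes obtained by linkage.

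The cost is some wording and extra analysis, with no new data collection. The result for this outcome may look less favourable.
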